##### Effectiveness Regarding New HIV/STI Diagnoses

We will also track STIs and new and previously known HIV diagnoses in the jail among priority groups and the general jail population. STI positivity will be calculated as positive tests per the total number of tests completed. New HIV diagnosis rates will be calculated as confirmed positive test results in persons without a prior diagnosis of HIV per the total number of tests completed within a given time period. We will use an interrupted time series analysis using monthly data points to compare rates during the 24 months before and 24 months after our intervention is implemented. Our primary analysis will involve a comparison of the longitudinal rates before and after the intervention, and a mixed effects model for interrupted time series will be used as a secondary analysis. We will conduct linear regression analyses to determine if there is a significant difference in new HIV diagnosis rates before and after the intervention.

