##### Sustainment

Sustainability refers to the extent to which a new practice is maintained or institutionalized within a setting’s ongoing operations [86]. We will assess how well the strategy components are maintained as part of existing jail processes for 6 months after the formal 24-month study period, including tracking retention in PrEP care for up to 6 months (through navigator follow-up). Our research team includes dissemination consultants, who are medical providers working in jails in Austin, TX; Chicago, IL; and Boston, MA, and who will offer input on refining our strategy components for ongoing use at the DCJ and the potential transfer and integration into other jail settings.

For PrEP linkage, current rates of linkage are essentially zero. Thus, in lieu of a pre/post comparison, we will report the proportion of patients linked to PrEP care during the implementation period with 95% CIs. Power analysis is performed for the interrupted time series analysis of monthly HIV positivity rates, assessing the difference in the mean between the 24 months before and after implementation. Over the preimplementation period, an anticipated 250 tests will be performed monthly with 3 new HIV diagnoses per month. In the postimplementation period, of 500 HIV tests per month, an increase to 9 new diagnoses per month is anticipated due to the focus on individuals identified by the prediction model as being at increased HIV risk. Furthermore, we assume a correlation of 0.2 among monthly observations. Based on a mixed effects Poisson regression model, we can detect the difference in the mean HIV-positive rate between the 2 periods with >80% power at a 2-sided type I error of 0.05. We will also perform subgroup analyses, comparing testing rates by sex, age group, and race or ethnicity.

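### The stated power of more than 80% holds only if the assumed 0.2 correlation costs nothing; read as serial correlation, it gives about 69 to 78%

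*Protocol article*

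**What the plan says.** The power calculation is in the last paragraph of the Sustainment section under Aim 3. It is introduced with "Power analysis is performed for the interrupted time series analysis of monthly HIV positivity rates", and the same sentence goes on to define the contrast as the difference in means between the 24 months before and after implementation. The inputs are:

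- before implementation: "an anticipated 250 tests will be performed monthly with 3 new HIV diagnoses per month";
- after implementation: "In the postimplementation period, of 500 HIV tests per month, an increase to 9 new diagnoses per month is anticipated";
- dependence: "Furthermore, we assume a correlation of 0.2 among monthly observations".

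The model named is a mixed effects Poisson regression. The result is that "we can detect the difference in the mean HIV-positive rate between the 2 periods with >80% power", at a two-sided type I error of 0.05. The text does not say whether the 0.2 is serial, exchangeable or induced by a random intercept, and it does not name the random effects.

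The section on effectiveness regarding new HIV/STI diagnoses defines the rate as confirmed new positives "per the total number of tests completed within a given time period". It makes the before/after comparison of longitudinal rates primary and a mixed effects interrupted time series model secondary.

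**The concern.** The data are one monthly series from one jail, analysed as an interrupted time series. In that setting, a correlation among monthly observations ordinarily means that neighbouring months resemble each other. Positive serial correlation widens the standard error of a before/after difference, so power must be lower than with independent months. Yet the printed figure is about what independent months give, with only a thin margin above 80%.

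This is the only power calculation in the article; PrEP linkage is to be reported as a proportion with a 95% CI and no test. If true power is nearer 70%, a null result on new diagnoses would be read as better-powered evidence than it is. Ignoring the correlation in the test does not solve this. Under first-order autocorrelation of 0.2, a simulated test that ignores it still rejects about 82% of the time, but its type I error is then about 11% and not 5% (shown below).

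**Working it through.** **Inputs.** From the Sustainment section: 3/250 and 9/500 per month, correlation 0.2, two-sided 0.05. From both sections: 24 months before and 24 after. Totals:

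- before: 24 × 3 = 72 diagnoses in 24 × 250 = 6,000 tests, 1.2%;
- after: 24 × 9 = 216 diagnoses in 24 × 500 = 12,000 tests, 1.8%;
- rate ratio 1.8/1.2 = 1.5; difference 0.6 percentage points.

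**Reproducing the plan's figure, no correlation penalty.**

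- Log-rate scale: log(1.5) = 0.405; SE = √(1/72 + 1/216) = 0.136; z = 2.98; power = Φ(2.98 − 1.96) ≈ 84.6%.
- Rate difference: SE = √(0.012/6,000 + 0.018/12,000) = 0.00187; z = 0.006/0.00187 = 3.21; power ≈ 89.4%.

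Other methods (two proportions, square-root scale, t test on monthly rates, simulated Poisson regression) fall between 86% and 88%. So more than 80% is reproduced when the 0.2 costs nothing.

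**Adding 0.2 as serial correlation.** For a mean of n = 24 months with AR(1) correlation ρ, the variance is multiplied by 1 + 2Σ(1 − k/24)ρ^k, summed over k = 1 to 23. With ρ = 0.2 this is 1 + 2 × 0.237 = 1.47. For correlation at lag 1 only it is 1 + 2 × (23/24) × 0.2 = 1.38. The figures below use the full 48 × 48 covariance, which also counts the small covariance across the boundary between periods.

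| Structure of the 0.2 | SE, log rate | Power, log rate | Power, rate difference |
|---|---|---|---|
| None (independent months) | 0.136 | 84.6% | 89.4% |
| AR(1) | 0.165 | 69.3% | 75.6% |
| Lag 1 only | 0.160 | 71.9% | 78.1% |

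A simulation of correlated Poisson months under AR(1) 0.2, with the standard error inflated to match, gave 71%.

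**How much correlation the claim tolerates.** AR(1), log-rate scale: ρ = 0.05 gives 81.1%, 0.06 gives 80.4%, 0.10 gives 77.4%, 0.20 gives 69.3%. Power falls below 80% once ρ exceeds about 0.06, under a third of the assumed value.

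**Type I error if the correlation is ignored.** The true SE is 0.1646/0.1361 = 1.21 times the nominal one, so the critical value 1.96 acts as 1.96/1.21 = 1.62. The two-sided tail beyond 1.62 is about 10.5%.

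**A random intercept shared by all 48 months.** It adds the same constant to every monthly log rate, so it drops out of the difference between periods and power stays at 84.6%. With one jail there is one draw of that intercept, so its variance cannot be estimated from the study's data.

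**The secondary model, for information.** Assumption: a step of the same size (rate ratio 1.5), fitted by generalised least squares to 48 monthly log rates, with a common trend or a slope change. With independent months the SE is about 0.245 to 0.272 and power 31 to 38%. With AR(1) 0.2 the SE is about 0.286 to 0.317 and power 24 to 29%. Simulated Poisson regression gave similar or slightly lower values (29 to 37% and 21 to 28%).

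**The case against.** The strongest reply is that the figure reproduces and that the article never says the 0.2 is serial. It names a mixed effects Poisson model, in which a correlation among observations can be read as a common one. With a shared random intercept, power is 84.6%. With a constant 0.2 across all 48 months it is 94% on the rate-difference scale. A condensed article may also leave the random-effects specification to the full protocol.

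Much of this stands. A reader might infer that the printed power is simply wrong under the plan's own correlation; the documents do not support that without a statement of structure. The reply has limits, though. A strict constant 0.2 across all months gives 70% on the log-rate scale that a Poisson model uses. In the readings that keep power above 80%, the 0.2 either has no effect or raises power, which is an odd role for an assumption stated as a feature of the data. And the article itself prints the inputs, the correlation and the power, so their consistency can fairly be asked about.

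Three further inferences go too far:

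- **Power as low as 24%.** That results if months are exchangeable at 0.2 within each period and independent across the boundary (variance factor 1 + 23 × 0.2 = 5.6, SE 0.322). Nothing in the article suggests that structure.
- **The claim fails because a trend-adjusted step has only 24 to 38% power.** The article powers the difference in means, which matches its primary comparison. The step belongs to the secondary model, so those figures do not recompute the stated one. The 31 to 38% part also assumes independent months.
- **The trial will have 11% type I error.** The article does not say that its test will ignore the correlation.

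In the other direction, comparing raw counts (3 against 9 per month) would give 93% or more under every structure tried, but the endpoint is defined per test completed.

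**Conclusion.** The point holds in conditional form. Power above 80% follows from the stated inputs only if the 0.2 correlation carries no penalty. Under serial correlation, the usual reading for one jail's monthly series, power for the before/after mean is about 69 to 76% (AR(1)) or 72 to 78% (lag 1 only), below 80% on both scales. Against the 85 to 89% obtained without a penalty, that is a loss of roughly 11 to 15 percentage points.

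This rests on the article's own rates and period lengths, on Poisson variation within months, and on reading the 0.2 as serial. The structure is unstated, so the defect is a power figure that does not follow from its inputs under the usual reading; it is not a proven arithmetic slip. Introducing the calculation as one for the interrupted time series adds to the ambiguity, although the contrast is then defined correctly as a difference in means.

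**What to change.** Revise the power paragraph in the Sustainment section:

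1. Name the correlation structure behind the 0.2 and the random effects in the Poisson model. If a shared random intercept is meant, say that it cancels from the before/after comparison and so does not affect power.
2. Restate power for a rate ratio of 1.5 (1.2% against 1.8%): about 85% without serial correlation, and about 70% (log-rate scale) to 76% (rate difference) with first-order autocorrelation of 0.2.
3. State that the figure applies to the before/after mean, the primary comparison. Add that a trend-adjusted step of the same size in the secondary interrupted time series model would have about 24 to 29% power under first-order autocorrelation of 0.2, and 31 to 38% with independent months.

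The cost is one paragraph of text and a less favourable stated figure if the 0.2 is serial. No more participants and no change to the design are needed.

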##### Evaluation of Qualitative Effects

We will also evaluate the qualitative effects of our implementation strategy through structured observations and discussions at the DCJ to assess changes (positive or negative) in knowledge and opinions of PrEP, workflow, and cross-agency collaboration in line with Dallas County’s goal of a coordinated HIV response [93]. Observations will be conducted by individuals with postgraduate training in qualitative methods who have undergone additional training with the DCJ and Parkland Health and who are approved to conduct observations under the protocol approved by the IRB at UT Southwestern Medical Center. Observations will be focused on specific interactions pertinent to the research questions (eg, between the navigator and person soon to be released). Qualitative data on effectiveness and implementation outcomes will be rapidly analyzed in real-time using structured analysis of field notes from observations and discussions. The resulting iterative findings will be presented to a study advisory panel every 4 months to assess evolving attitudes and practices surrounding HIV testing and PrEP (ie, acceptability), gather perceptions of feasibility and penetration of the intervention, and solicit feedback about the ways to improve outcomes.

#### Ethical Considerations

Each aim of the study has undergone a separate review of procedures and protocols by the UT Southwestern Medical Center IRB, with details of human subject protection outlined in the protocol by aim. This IRB has a prisoner representative, and all IRB-approved protocols were reviewed by Parkland Health and approved by the DCJ correctional health leadership before beginning study activities. To date, the IRB has approved the protocols for aim 1 (STU 2021-0763) and aim 2 (STU 2021-1172). In addition, the Office of Human Research Protection has reviewed and approved the inclusion of prisoners in human subject research for the overall study protocol in 2022.

For all participants in focus groups and individual interviews in aim 1, the research team has obtained verbal consent. To ensure informed consent, researchers also provided information about the nature and purpose of the study, confidentiality and privacy, HIPAA (Health Insurance Portability and Accountability Act) regulations, potential risks, discomforts and benefits of participation, and the option not to participate or start then stop participating in the interview at any time. In addition, stakeholders were encouraged to contact the study team at any time with questions or concerns they may have about the study. Eligible participants (ie, individuals not employed by UT Southwestern or Parkland Health according to institutional policy) were paid US $25 as compensation for their time for each interview or focus group attended.

Regarding EHR usage for aim 2, all study data were collected from existing EHRs, including medical intake forms at the DCJ and EHRs from Parkland Health and Hospital Systems, to identify potentially eligible subjects for the research. Records were matched based on multiple variables, including patient name, preferred name, date of birth, gender, biological sex, race or ethnicity, and social security number, as available. The medical record data include data collected as part of the medical intake process at the jail and routine clinical care at the jail and Parkland, including demographics, information from clinical encounters, prescription information, laboratory tests and results, and billing information. For those who did not receive medical care or treatment at Parkland Health, only data from the jail EHR were used. There was no additional direct collection of specimens, records, or data from subjects, and the IRB approval allowed secondary analysis without additional consent to identify research subjects and build the prediction model.

Data are not deidentified, as individuals meeting the basic eligibility criteria will be contacted by the researchers for recruitment into the study. No additional research procedures or continued access to identifiable private information will occur until after subjects have given valid consent to participate in the research study. The risk of this activity is minimal to the subjects because the information collected will be limited only to information allowing researchers to determine eligibility for the study and contact information. Only the minimum information necessary to determine eligibility will be recorded. Researchers have been granted access to the medical record data by the institutions and will protect the data they use and record for this activity according to institutional and HIPAA standards for protecting privacy and maintaining confidentiality. If the subjects identified decline participation in the research, the data collected will not become part of the research data. If subjects agree to participate in the research, the identifiable data collected will become part of the subjects’ research records and will be stored according to the research confidentiality plan. Because of the nature of the detailed inclusion criteria, it is not feasible for researchers to advertise and screen for eligible subjects. The Office of Human Research Protection highlights this as an acceptable activity to waive informed consent to permit investigators to obtain and record identifiable private information for the purposes of identifying potential subjects [94].

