##### Validation of the HIV Risk Prediction Model

We will use our prior models for predicting incident HIV [73,74] to identify candidate variables for our HIV prediction model. Subsequently, the use of temporal validation will assess how well our model will perform prospectively, dividing our dataset into a derivation dataset (2015-2021) and a validation dataset (2022-present). We will train our model to predict incident HIV diagnoses, defined as positive HIV screening and confirmatory tests or new HIV diagnosis codes without prior evidence of HIV in the EHR [73-75]. We will have ample data on new HIV diagnoses to train our models, as Parkland has a robust HIV testing program and diagnoses more new cases of HIV than any other entity in Dallas [76]. Jail EHR data may be more limited in scope because the jail generally provides short-term episodic care. However, given high recidivism rates [77], many incarcerated individuals will have multiple data points in the jail EHR to inform HIV risk prediction, including data on prior HIV/STI testing and substance use.

We will compare the performance of parsimonious versus full models in the validation dataset based on their ability to discriminate between patients with and those without incident HIV using the C-statistic or area under the receiver operator characteristic curve and the Hosmer-Lemeshow goodness of fit test. Additionally, we will use multiple complementary approaches for estimating HIV risk to capture the greatest number of individuals with indications for PrEP. This will include anyone who identifies as transgender, requests MSM housing, has had a recent STI, or opts-in for HIV/STI testing, in addition to those flagged by our EHR model. We will compare EHR models against these criteria to measure the added value of each approach (eg, number of individuals identified by our model as likely to benefit from PrEP who are missed by patient-reported data and vice versa).

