**Figure 2 figure2:**
[figure not shown]
Intervention steps in the jail-to-community continuum. DCJ: Dallas County Jail; EHR: electronic health record; PrEP: pre-exposure prophylaxis; STI: sexually transmitted infection.

In the “identify” step, when individuals enter the jail, a jail EHR record will be created (or an existing record will be opened for those with prior DCJ incarceration). Our automated algorithm will match the jail EHR to the Parkland EHR and generate an individual HIV risk score. For people with predicted HIV risk above a prespecified threshold that maximizes sensitivity without causing alert fatigue among providers, an automated prompt will appear in the jail EHR for providers to discuss PrEP and order HIV/STI testing. As illustrated in Figure 2, providers will also be prompted to order HIV/STI tests for any patients who report risk factors at intake or during a clinical assessment (eg, transgender identity and requests to be housed with MSM) or who request testing directly. Prompts will persist until orders are completed as a “nudge,” a behavioral economic intervention to maximize ordering [83], and results are entered into the EHR.

In the “engage” step, positive HIV tests will prompt referrals to the jail HIV clinic for rapid initiation of antiretroviral therapy according to the current practice, and STIs will be treated based on CDC guidelines [84]. Persons with negative HIV tests will meet one-on-one with a provider or PrEP navigator and receive counseling informed by our PrEP decision-support tool. The navigator we hire will be experienced in working with CL-involved people. Counseling will be person-centered and culturally tailored, with positive sexual health framing.

In the “navigate” step, for patients interested in PrEP, the navigator will review a list of PrEP clinic locations and assist with selecting a provider. Once an individual is released from the DCJ, the navigator will facilitate PrEP linkage by contacting that individual (by phone or SMS text messaging) and providing personalized care navigation. A hotline will be available for released individuals to call for assistance with PrEP referrals. The navigator will continue to follow referred patients for 3 months after any PrEP initiations, recording these contacts and clinical outcomes in REDCap, a secure online data capture system [85].

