##### Feasibility

Feasibility refers to the extent to which a practice change can be successfully used or carried out within a specific setting [86]. We define feasibility as >65% of eligible patients being offered HIV/STI testing and one or more PrEP discussions, our patient PrEP decision-support tool, a PrEP navigation visit, or a PrEP referral in jail.

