##### Acceptability

Acceptability refers to the perception among setting stakeholders that a practice is agreeable, palatable, or satisfactory [86]. We will calculate the proportions of patients who accept offers for one or more HIV testing, STI testing, PrEP discussion, navigator contact, or PrEP referral, with acceptance of >80% of test offers and >65% of discussion offers considered acceptable based on prior studies [35,87-89]. We will evaluate differences in feasibility and acceptability among patients by age, sex, gender identity, and race or ethnicity to identify imbalances in the offering and uptake of testing and referrals.

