### Potential Limitations and Alternative Approaches

In the process of refining the implementation strategy in our second aim, EHR models may be hampered by limited or missing data. We will minimize the missingness of EHR data by combining jail and Parkland data and extending this dataset over a 10-year timespan. We will explore the use of the missingness of EHR variables (which may be a proxy for not being engaged in primary care) as indicators to understand the effect on model performance. If model performance is suboptimal, we will rely primarily on patient-reported data to identify HIV risk. For EHR alerts, we will proactively address potential alert fatigue [95] by employing rigorous user-centered design principles [96]. We will also train providers on how to respond to alerts about HIV risk, as providers may be unaccustomed to these.

Delays in the generation of electronic HIV risk scores could result in the identification of individuals likely to benefit from PrEP after their release from jail. If this occurs, we expect to identify many of these individuals using patient-reported data. However, the model we have developed will generate scores on day 3 of each person’s incarceration, which will mitigate delays. We will also generate future EHR prompts for HIV/STI testing and PrEP if the patient returns to jail, and the navigator will contact the patient to encourage HIV testing and PrEP evaluations with community providers. Though patients may decline visits to discuss PrEP, we will maximize patient interest by training staff to present PrEP in a positive, discreet, and patient-centered manner and will offer our decision-support tool for patients to review independently. Since barriers, such as medical mistrust, transportation, and anticipated stigma, may limit patients’ access to PrEP, we will hire and train a navigator who is able to build rapport with diverse populations, use principles of trauma-informed care [97-99], and teach at many education levels. Additionally, we will access existing resources, such as care coordination, offered by community partners.

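### The >80% test-acceptance criterion includes people who joined the risk group by asking for the test, and the rule on decliners' data must be reconciled with the >65% discussion criterion

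*Protocol article*

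**What the plan says.** The Acceptability section (aim 3) counts the patients who accept what they are offered, "acceptance of >80% of test offers and >65% of discussion offers considered acceptable based on prior studies". It also plans comparisons by age, sex, gender identity and race or ethnicity. Table 1 restricts its metrics to patients with high risk and lists completed HIV/STI testing as an acceptability metric.

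The section on validating the prediction model defines who is at increased risk. Besides transgender identity and a request for MSM housing, the group takes in anyone who "has had a recent STI, or opts-in for HIV/STI testing, in addition to those flagged by our EHR model". Steps for Strategy Implementation likewise prompts a test order for patients who ask for testing. Study Setting says every entrant is given the opt-in choice at intake.

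On people who decline, Ethical Considerations says: "If the subjects identified decline participation in the research, the data collected will not become part of the research data". In aim 3, under Steps for Strategy Implementation, the navigator asks for verbal consent before holding the sexual health discussion and before making contact after release.

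**The concern.** Two of the protocol's numeric targets may not measure what they are meant to measure.

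The first is test acceptance. A person who opts in for a test enters the risk group because of that choice and, once tested, counts as having accepted. For that person, entry criterion and outcome are nearly the same event. The pooled rate then mixes willingness among people approached because of their risk with the near-certain uptake of people who asked. Only the first says whether the strategy is acceptable.

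The second is discussion acceptance. Consent to the navigator's discussion is sought at the point where the offer is accepted or refused. If declining means that a person's data are not kept, the refusals that belong in the denominator disappear. The demographic comparisons would suffer too, because they need the characteristics of those who refused.

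At stake is a target that is reported as met while acceptance among the people the strategy set out to reach is below it.

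**Working it through.** The targets come with no assumed rates, so there is no figure of the plan's own to reproduce. The check is algebra on the two ratios. The protocol gives neither the share of requesters nor any refusal rate, so the rates below are assumptions chosen to show a range.

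**Test acceptance (target >80%).** Let r be the share of the risk group that asked for the test, accepting at about 100%, and b the acceptance among the rest. Then

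pooled acceptance = r + (1 − r)b,

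which exceeds 0.80 when r > (0.80 − b)/(1 − b).

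- b = 0.50: 0.30/0.50, so r must exceed 60%. At exactly 60% the pooled rate is 0.60 + 0.40 × 0.50 = 0.80, which does not pass.
- b = 0.60: 0.20/0.40, so r must exceed 50%.
- b = 0.70: 0.10/0.30, so r must exceed about 33%.
- b = 0.75: 0.05/0.25, so r must exceed 20%.

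The pooled rate is always above b when r > 0, but whether it crosses 80% depends on r. If b is already above 80%, requesters do not change the conclusion.

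**Discussion acceptance (target >65%), only if refusals are dropped.** Let a be true acceptance and d the share of refusals not retained. Then

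observed acceptance = a / [a + (1 − a)(1 − d)],

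which exceeds 0.65 when d > 1 − 0.35a/[0.65(1 − a)].

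- a = 0.40: 1 − 0.14/0.39, so d above 64%.
- a = 0.50: 1 − 0.175/0.325, so d above 46%.
- a = 0.60: 1 − 0.21/0.26, so d above 19%.
- d = 1 gives 100% whatever a is.

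**Does the decliners' rule reach aim 3?** The passages point both ways.

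- The paragraph before it concerns EHR use in aim 2, and the rule itself sits among text on information used to determine eligibility. That suggests screening records only.
- The same text says that people found in the records will be contacted for recruitment and may decline. Aim 2 uses existing data under a waiver, and aim 1 recruits former inmates by referral or flyer. Only aim 3 approaches EHR-identified people and asks for consent.

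**Feasibility (target >65%).** Dropping people who were offered and declined works in the opposite direction. With a true offer rate f and acceptance a, the rate becomes (f − D)/(1 − D), where D = f(1 − a). For f = 0.70 and a = 0.65, D = 0.245 and the rate falls to 0.455/0.755 = 60%.

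**The case against.** On requesters, no passage says that an unsolicited request is scored as an accepted offer, and the final process for identifying candidates is still to be selected. The first point is weak: all entrants are given the test option at intake, and Table 1 counts completed tests among high-risk patients, so on an ordinary reading requesters are included. The second point means that the change can still be made easily.

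On decliners, the text follows on from aim 2, and the aim 3 consent passage says nothing of discarding refusals. Table 1 lists offers and completions separately, discussions may be held by a provider instead of the navigator, and a proportion of offers accepted presupposes that offers are counted. This stands as far as it goes: the protocol does not say that aim 3 refusals are deleted. It leaves two passages that must be reconciled.

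A reader might go further and infer that the feasibility target is met by construction. It is not. "We define feasibility as >65% of eligible patients being offered HIV/STI testing and one or more PrEP discussions" requires a PrEP element (a discussion, the decision tool, a navigation visit or a referral) as well as a test offer, so near-universal test offers cannot pass it alone, and losing offered decliners lowers the rate.

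A reader might also infer that people released before the risk score is available are never flagged, because "the model we have developed will generate scores on day 3 of each" person's stay. The limitations section names that risk and gives patient-reported identification, prompts on return to jail and navigator contact as backups. Steps for Strategy Implementation links the score to jail entry but gives no time for it, so day 3 does not clearly contradict it.

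**Conclusion.** The concern holds for test acceptability. The >80% criterion is applied to a group partly selected on the outcome, and the pooled rate overstates acceptance among those who did not ask. With requesters at about 100% and others at 60% to 75%, a requester share above 50% down to above 20% is enough to pass. The direction of the bias rests on requesters accepting more often than others. Its size rests on rates that the protocol does not give.

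For discussion acceptability, the finding is an unreconciled conflict, not an established bias. It would matter only if the decliners' rule covers aim 3. In that case, losing about half the refusals at a true acceptance of 50% would be enough to pass.

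The documents support no finding that feasibility passes automatically. The one open question is whether people released before the day-3 score count among eligible patients, a term that the Feasibility section leaves undefined. For scale, take 70% offered among those who stay and 10% to 40% released early. Counting the early-released gives 63% to 42% if none of them is offered anything, and 68% to 62% if half are. These shares are also assumed.

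**What to change.** 1. Apply the >80% test-acceptance target only to people flagged by another route (the model, transgender identity, MSM housing request, recent STI) who had not requested the test. Report requesters separately. This costs a smaller denominator and a less favourable headline rate; no new data collection is needed provided that the route of entry is recorded.
2. State in Ethical Considerations that the decliners' rule covers recruitment-screening records only. State also that offer and accept/decline indicators, with demographic strata, are kept in de-identified form for everyone offered a discussion, so that refusals stay in the >65% denominator and in the planned comparisons. This belongs under aim 3 ethics approval and not under the aim 2 waiver. The article lists approval to date only for aims 1 and 2, so the cost is wording in the aim 3 submission.
3. Say in one sentence whether people released before the day-3 score count in the feasibility denominator.
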